#### Randomisation

##### Practice allocation

Practices will be stratified by practice size (less than two or two or more whole-time-equivalent GPs) and presence of existing structure primary diabetes care service. They will then be allocated to intervention or control groups using minimization [34]. Allocation will be carried out independently of the research team. It will occur prior to patient identification and baseline data collection. While it is regarded as best practice to randomize after baseline data collection, in this study allocation must take place in this sequence to facilitate the recruitment of peer supporters from the patient register in intervention general practices before the randomisation of patients and the beginning of the intervention.

##### Patients: random selection

Once a complete diabetes register is established, the project manager assists the practices in using a list of random numbers to select patients for participation. All patients on the register are allocated a number 1 to Y (where Y is the total number of patients on the list). Randomly selected patients are sent an invitation letter, information sheet and reply slip. Patients who do not respond in two weeks are contacted by telephone by the practice nurse to ascertain interest in participation. If a patient does not meet the eligibility criteria or declines to participate the next patient is selected from the list until the quota of 21 is reached. (Figure 1)

**Figure 1 F1:**
[figure not shown]
Flow of practices and patients throughout the trial.

Basic characteristics of patients who decline to participate will be collected including date of birth, sex, GMS status, duration of diabetes and reason for not participating.

#### Sample size calculation

The study aims to achieve a sample of 410 patients from 20 practices. This takes into account the effect of cluster randomisation and allows for 80–85% patient follow up and a 15% practice attrition rate (though the authors previous experience of cluster randomized trials in this setting indicate much lower patient and practice attrition rates [10]). Sample size calculations are based on a 20% improvement from baseline in the control group and 50% improvement in the intervention group [35]. All calculations are two-sided and based on an alpha of 5% and a power of 80%.

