##### Systolic Blood pressure (SBP)

46% of patients, in a previous study in Dublin, have a SBP >160 mmHg [10]. This level of SBP represents very poorly controlled blood pressure as the current upper recommended limit for an individual with type 2 diabetes is 130 mmHg [36]. The intracluster coefficient (ICC) for SBP is 0.001 [10]. A sample size of 400 patients from 20 practices is needed to show a significant improvement in the proportion of patients with a SBP below 160 mmHg (i.e. 50% improvement in intervention group and 20% improvement in control group as above).

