##### Cholesterol

57% of patients have a total cholesterol >5 mmol [10], which is the upper recommended limit for patients with type 2 diabetes [38] (ICC = 0.06) [10]. A sample size of 410 patients from 20 practices is needed to show a significant improvement in the proportion of patients with a cholesterol <5 mol/l.

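### The 410 patients do not give 80% power on every primary outcome after the patient and practice losses that the protocol says they allow for

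*Protocol article*

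**What the plan says.** The section on sample size calculation in the protocol article gives the target: "The study aims to achieve a sample of 410 patients from 20 practices". The claim made for that total is: "This takes into account the effect of cluster randomisation and allows for 80–85% patient follow up and a 15% practice attrition rate". A parenthesis adds that the authors' "previous experience of cluster randomized trials in this setting indicate much lower patient and practice attrition rates", without giving a figure. For effect size, "Sample size calculations are based on a 20% improvement from baseline in the control group and 50% improvement in the intervention group". Throughout, the section uses a two-sided 5% level and 80% power.

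The outcome subsections then give separate requirements:

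- **SBP:** 46% above the threshold of 160 mmHg, ICC 0.001. "A sample size of 400 patients from 20 practices is needed to show a significant improvement in the proportion of patients with a SBP below" that threshold.
- **Cholesterol:** 57% above 5 mmol, ICC 0.06. "A sample size of 410 patients from 20 practices is needed".
- **HbA1c:** difference 0.9, SD 1.6, ICC 0.001; 130 patients from 8 practices.
- **Well-being:** difference 5, SD 10.3, ICC 0.07; 221 patients from 12 practices.

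The section on random selection of patients sets a quota of 21 per practice, so at most 420 would be enrolled.

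**The concern.** The trial total equals the largest single-outcome requirement, the one for cholesterol. The two losses that it is said to absorb are large if they multiply: 15% of practices lost, and 80–85% follow-up in the rest, keeps only 68–72% of patients. Whether 410 has that much room can be tested from the figures printed in the section.

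Blood pressure and cholesterol are listed as primary outcomes, and they set the size of the trial. If the stated power is not there, a null result on either would be read against a nominal 20% chance of missing the assumed effect when the real chance is higher.

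**Working it through.** **Inputs.** All come from the sample size section, except 1:1 allocation, which is an assumption because no ratio is stated. Average practice size is 410/20 = 20.5.

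**Formulas.** For two proportions, patients per arm before clustering are n = [1.96√(2p̄(1−p̄)) + 0.8416√(p₁(1−p₁)+p₂(1−p₂))]² / (p₁−p₂)². For two means, n = 2(1.96+0.8416)²SD²/difference². The design effect is DE = 1 + (m−1)×ICC, with m patients analysed per practice. Power uses the same expressions with n = (analysed patients/2)/DE. No continuity or small-sample correction is applied.

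**1. Can the stated figures be reproduced?** Take improvement as a relative fall in the uncontrolled share.

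- **SBP:** 46% × 0.8 = 36.8% and 46% × 0.5 = 23.0%. n = (1.269 + 0.539)²/0.138² = 171.6 per arm, or 343 in total. × DE 1.0195 = 350 analysed. Dividing by 0.85 gives 412, and multiplying by 1.15 gives 402. The stated 400 therefore fits one 15% allowance.
- **HbA1c:** 2 × 49.6 = 99.2; × DE 1.015 (130/8 = 16.25 per practice) = 101. Dividing by 0.80 gives 126, close to the stated 130.
- **Cholesterol:** 57% × 0.8 = 45.6% and 57% × 0.5 = 28.5%. n = (1.339 + 0.566)²/0.171² = 124.0 per arm, or 248 in total. × DE 2.17 = 538 analysed before any loss. The stated 410 is not reproduced.
- **Well-being:** 2 × 66.6 = 133.2; × DE 2.22 (221/12 = 18.4 per practice) = 296, so the stated 221 is not reproduced either. The 410 total still exceeds this need (see the table).

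**2. What is left after both losses?** 20 × 0.85 = 17 practices. 0.85 × 0.80 = 0.68 and 0.85 × 0.85 = 0.7225. From 410 that leaves 279–296 patients, and from 420 it leaves 286–303.

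**3. Power at 410 enrolled.** Example, SBP with 80% follow-up in 17 practices: m = 16.4, DE = 1.0154, n = 278.8/2/1.0154 = 137.3. (0.138√137.3 − 1.269)/0.640 = 0.544, so power is 70.7%.

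| Outcome | No loss | 15% of patients lost, 20 practices | 15% of practices lost, no other loss | Both losses |
|---|---|---|---|---|
| SBP, fall in uncontrolled share (36.8% v 23.0%) | 86% | 80% | 80% | 71–73% |
| Cholesterol, fall in uncontrolled share (45.6% v 28.5%) | 68% | 65% | 61% | 57–58% |
| SBP, rise in controlled share (64.8% v 81.0%) | 96% | 92% | 92% | 86–88% |
| Cholesterol, rise in controlled share (51.6% v 64.5%) | 43% | 41% | 38% | about 35% |
| HbA1c | >99% | >99% | >99% | >99% |
| Well-being | 89% | 87% | 84% | 80–81% |

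The controlled-share rows start from 54% (SBP) and 43% (cholesterol), multiplied by 1.2 and 1.5. With 420 enrolled, the first two rows become 72–74% and 57–59% after both losses.

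**4. If 80–85% is overall follow-up.** Suppose it already includes patients of lost practices, so that 328–349 of 410 are analysed. SBP (fall) then has 78–80% and cholesterol (fall) 64–65%, with the analysed patients spread over 20 practices. If they sit in 17 practices, SBP is 77–80% and cholesterol 60–61%.

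**The case against.** Several points on the other side stand.

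- **An allowance was made somewhere.** Because 410 equals the largest stated requirement, a reader might infer that nothing was added for attrition. The figures contradict that: SBP is set at 400 against about 350, and HbA1c at 130 against about 101. An allowance can sit inside the outcome figures.
- **The SBP shortfall depends on the reading.** The SBP subsection speaks of the proportion below 160 mmHg. Taken literally, the improvement is a rise in the controlled share, and SBP then survives both losses.
- **Multiplying the losses is an interpretation.** The protocol does not say whether 80–85% applies only within retained practices. If it is the overall figure, SBP power is close to 80%.
- **Cholesterol is mainly an ICC problem.** Its design effect of 2.17 turns a need of 248 into 538. Attrition takes power from 68% to 57–58%, but the stated 410 is already short without it.
- **Lower attrition is expected, and stopping the intervention is not loss.** The data analysis section includes all randomised patients regardless of participation, so a further rule to that effect would largely repeat what is there.

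These points narrow the concern but do not remove it. The reading that rescues SBP makes cholesterol much worse (43% with no loss). The overall-follow-up reading leaves cholesterol at 65% or below. The expectation of lower attrition has no figure and does not withdraw the statement that both losses are allowed for.

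**Conclusion.** The statement that 410 patients allow for both losses at 80% power is not correct for every primary outcome. No reading tested gives 80% on both SBP and cholesterol.

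Cholesterol falls short on every reading, including with no attrition, so at the stated ICC its 410 contains no attrition allowance. For SBP the shortfall is conditional. It is 7–9 percentage points if improvement is a fall in the uncontrolled share and the losses multiply, at most about 3 points if 80–85% is overall follow-up, and nil if improvement is a rise in the controlled share.

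A reader might infer that two of the four primary outcomes fail outright because of attrition. The documents do not support that: SBP fails only on some readings, and the cause for cholesterol is mainly clustering. HbA1c and well-being keep 80% after both losses.

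The figures rest on 1:1 allocation, equal practice sizes and normal-approximation formulas. A continuity correction would raise the SBP requirement to about 379.

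**What to change.** In the sample size section:

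1. State whether the 20% and 50% improvements apply to the uncontrolled or the controlled proportion, and use that reading for both SBP and cholesterol.
2. State whether 80–85% follow-up applies within retained practices, so that the losses multiply, or is the overall figure.
3. Withdraw the claim that 410 allows for both losses at 80% power.
4. Add a table of power for each primary outcome with no loss and after the stated losses. Name the base: 279–296 analysed from 410, or 286–303 if the quota of 21 per practice yields 420.

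The cost is protocol wording and one small table. No increase in enrolment is required. On the least favourable SBP reading, 350/0.7225 to 350/0.68, about 485–515 enrolled, would be needed to cover both losses. That shows the size of the gap and is not a proposed target.

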##### 1. Peer supporters

Potential peer supporters are identified by GPs and practice nurses in the intervention practices. Peer supporters are recruited and trained at a ratio of approximately one peer supporter to seven/eight patients with type 2 diabetes. They are eligible to be trained if they meet the following inclusion criteria:

• They have had type 2 diabetes for at least one years duration

• They participate in preventive treatments and are generally adherent to treatment and behaviour change regimens, as judged by the practice team

• They have a capacity and commitment to undergo the training required (outlined below)

• They have a full understanding of the importance of patient confidentiality

• They undertake to liaise with the practice nurse and/or GP if unanticipated problems arise during the course of their peer support activity

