## Discussion

Diabetes self management training has traditionally been delivered in a didactic manner with emphasis on imparting knowledge. However this approach has been shown to be ineffective in changing the behaviour of individuals with type 2 diabetes and improving metabolic control [51]. An alternative approach such as peer support may improve these outcomes. This approach is based on a social support theoretical framework rather than an educational or psychological framework and the outcomes we have selected for the study reflect this underlying theoretical framework. The potential advantage of peer support is that it focuses on the impact of the illness on daily life rather than on medical information about illness. The group meeting components of the intervention in this study are designed to build on the lay element of peer support through the encouragement of the sharing of experiences and exchanges between participants. Peer support is a complex intervention and a strength of this study has been the use of the MRC Framework for the evaluation of randomized controlled trial of complex interventions designed to improve health outcomes [24]. Details of the initial phases of the framework leading to the finalisation of this protocol are presented elsewhere. (BMC Health Services Research, in press). The study is specifically based in the general practice setting and empowers and supports practice staff in the recruitment of participants and peer supporters and data collection. This approach embeds the study in the real world of primary care and will increase the generalisability of results. An additional strength of the study is its duration of two years, which allows us to test the sustainability of a peer support intervention in a clinical setting over time.

Peer supporters are central to the study and methods of supporting them in their role have been identified. The project manager is a source of advice and support for peer supporters. They are also encouraged to turn to their GP and practice nurse who are the clinicians responsible for the care of all patients within each peer support group.

In summary, peer support is a complex intervention and evaluating such an intervention presents challenges to researchers. This study aims to determine whether a peer support programme for patients with type 2 diabetes improves biophysical and psychosocial outcomes and whether it is an acceptable, cost effective intervention in the primary care setting.

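### The SBP power allows for clustering by practice but not by peer group, a layer that exists only in the intervention arm

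*Protocol article*

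**What the plan says.** Under Sample size calculation: "The study aims to achieve a sample of 410 patients from 20 practices". The allowance for clustering is one sentence: "This takes into account the effect of cluster randomisation". The target also "allows for 80–85% patient follow up and a 15% practice attrition rate". For SBP, "The intracluster coefficient (ICC) for SBP is 0.001 [10", cited to an earlier study. HbA1c has the same value, cholesterol 0.06 and well-being 0.07, all from the same source. Each value is given once, with no distinction between arms.

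On delivery, the Abstract gives three peer supporters per intervention practice, and the section on peer supporters says: "Peer supporters are recruited and trained at a ratio of approximately one peer supporter to seven/eight patients with type 2 diabetes". With 21 patients per practice, that is three groups of about seven. Under Retention and support of peer supporters, a supporter who resigns is replaced from within the same group, and the replacement is named at the outset. Under Peer support meetings there are nine sessions over two years. The Discussion describes the purpose of the meetings as "encouragement of the sharing of experiences and exchanges between participants". Control practices deliver standardised care only, without groups.

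**The concern.** The design is partially nested. Patients lie within practices in both arms, and within peer groups inside practices in the intervention arm only. If the intervention works through a shared leader and exchange among members, as the Discussion intends, outcomes within a group should become more alike. An ICC from an earlier study, applied equally to both arms, makes no explicit allowance for that. The variance in the intervention arm would then exceed what the calculation assumes, and the stated 80% power would be somewhat favourable. SBP is the exposed outcome, because its practice ICC of 0.001 leaves no margin that could absorb a group effect by accident.

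**Working it through.** **Inputs from the protocol.** SBP above 160 mmHg at baseline 46%. The calculation is "based on a 20% improvement from baseline in the control group and 50% improvement in the intervention group", so the proportions are 46% × 0.8 = 36.8% (control) and 46% × 0.5 = 23.0% (intervention). Practice ICC 0.001; 20 practices; two-sided 5%; three groups per intervention practice.

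**Assumptions.** Practices split 10 and 10, which gives about 30 groups. Group membership is stable; this is inferred from the replacement rule and the meeting schedule. The protocol gives no group ICC, so 0.02, 0.05 and 0.10 are shown as a range.

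**Reproducing the stated figures.**
- SBP, pooled two-proportion formula: 344 patients before clustering. Design effect 1 + 19 × 0.001 = 1.019, giving 351. Allowing for 15% patient loss gives 351 × 1.15 = 403 or 351/0.85 = 412 (about 413 with this rounding), against the stated 400.
- HbA1c: 100 × 1.015 = 102; 102/0.80 = 127, against the stated 130.

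Both are matched closely by practice clustering and patient loss alone, with no group term.

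**Adding the group layer.** With m patients per practice:
- control design effect = 1 + (m − 1) × 0.001
- intervention design effect = 1 + (m − 1) × 0.001 + (m/3 − 1) × group ICC
- SE² = [0.368 × 0.632 × DE(control) + 0.230 × 0.770 × DE(intervention)] / n per arm
- power = Φ(0.138/SE − 1.96)

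At 410 × 0.85 = 348.5 patients with all practices retained, n = 174.25 per arm, m = 17.4, group size 5.8 and control design effect 1.016.

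| Group ICC | DE, intervention | SE | SBP power, N = 348.5 | SBP power, N = 400, no loss |
|---|---|---|---|---|
| 0 | 1.016 | 0.0489 | 80.6% | 85.6% |
| 0.02 | 1.113 | 0.0499 | 79.0% | 83.9% |
| 0.05 | 1.257 | 0.0513 | 76.7% | 81.4% |
| 0.10 | 1.497 | 0.0537 | 73.0% | 77.4% |

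Patients needed for 80% power before loss (same unpooled formula, m = 20): 344, 361, 385 and 427. Of the stated 400, that leaves 14% (1 − 344/400), 10%, 4% or nothing for loss.

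**Sensitivity to method.** A pooled-variance formula at 340 patients gives 79.0%, 76.9%, 73.9% and 69.2%, so somewhat larger losses. A simulation at 400 patients, with the group ICC on the latent scale and a practice-level t test, gives 82%, 79% and 77% at 0, 0.05 and 0.10, so smaller losses.

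**Other outcomes at 348.5 patients, group ICC 0 to 0.10.** HbA1c stays above 99%. Well-being goes from 87.1% to 83.4%. Cholesterol (45.6% v 28.5%, ICC 0.06) goes from about 66% to 62%. Cholesterol falls short without any group effect: 250 × (1 + 19 × 0.06) = 250 × 2.14 = 535 patients before loss, against 410 stated.

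**The case against.** The sentence on cluster randomisation is true as written: practices are the randomised units, and each outcome has a practice ICC. The text claims no allowance for treatment groups. This stands; the point is an omission, not a false statement.

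The size of the loss rests on an assumed ICC. At 0.02 it is one to two points. The 348.5-patient scenario also starts almost exactly at 80%, so nearly any penalty crosses the line. Without patient loss, SBP power stays above 80% up to a group ICC of about 0.05, and the protocol says attrition was much lower in the authors' earlier trials. All of this stands and limits the point. In the other direction, the scenario leaves out the 15% practice loss that the protocol also allows for.

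A reader might infer that the planned analysis is invalid because it ignores the groups. The documents do not support that. Groups lie wholly within practices, and Data analysis plans survey methods that adjust for design effects. If practice is the primary sampling unit, its standard errors absorb the group correlation. In a simulation, a practice-level analysis had type I error of 0.053 and 0.057 at group ICCs of 0.05 and 0.10. A peer-group term in the primary model is therefore a preference, not a correction.

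Group membership is also partly recoverable already, because supporters record who attends each meeting. That covers attenders only.

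**Conclusion.** The omission is real and modest. The sample size section gives the peer groups no term, although they exist in one arm only and are the intended means of effect. The consequence is for stated power, mainly for SBP: about 80.6% becomes 79.0%, 76.7% or 73.0% at an assumed group ICC of 0.02, 0.05 or 0.10, with 85% patient follow-up, no practice loss, an equal split of practices and stable groups. HbA1c and well-being keep more than 80% in that scenario.

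A reader might also infer that the groups are what makes 410 too few. They are not: cholesterol has only about 68–70% power at 410 before any loss or group effect, on the protocol's own ICC of 0.06. That discrepancy is separate and larger, and should be reconciled at the same time.

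**What to change.** 1. Restate the power under Sample size calculation, for SBP and for cholesterol, with an arm-specific design effect: the practice ICC in both arms, plus a stated sensitivity range for the peer-group ICC (for example 0.02 to 0.10) in the intervention arm only. Reconcile the cholesterol figure in the same revision.
2. Record a peer-group number for every intervention patient, including those who never attend, and report the group ICC with the results.
3. Keep practice as the cluster (primary sampling unit) in the primary analysis. A peer-group random effect, or a separate variance in the intervention arm, can be an optional sensitivity analysis.

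The cost is revised wording, one database field and one reported estimate. No extra patients are proposed. The downside is a stated SBP power a few points lower.

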##### Systolic Blood pressure (SBP)

46% of patients, in a previous study in Dublin, have a SBP >160 mmHg [10]. This level of SBP represents very poorly controlled blood pressure as the current upper recommended limit for an individual with type 2 diabetes is 130 mmHg [36]. The intracluster coefficient (ICC) for SBP is 0.001 [10]. A sample size of 400 patients from 20 practices is needed to show a significant improvement in the proportion of patients with a SBP below 160 mmHg (i.e. 50% improvement in intervention group and 20% improvement in control group as above).

##### HBA1c

A sample size of 130 patients from 8 practices is needed to demonstrates a clinically significant difference in mean HBA1c between intervention and control groups (i.e a difference of 0.9% [37], standard deviation 1.6; ICC 0.001 [10])

##### Cholesterol

57% of patients have a total cholesterol >5 mmol [10], which is the upper recommended limit for patients with type 2 diabetes [38] (ICC = 0.06) [10]. A sample size of 410 patients from 20 practices is needed to show a significant improvement in the proportion of patients with a cholesterol <5 mol/l.

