##### Well-being scores (WBS)

A sample size of 221 patients from 12 practices is needed to show a clinically significant difference in WBS between intervention and control groups (i.e. a mean difference of 5 points, standard deviation, 10.3; ICC of 0.07) [10].

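### At the protocol's own ICC, 410 patients from 20 practices give about 68% power for cholesterol, not 80%; the well-being figure of 221 is short in the same way

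*Protocol article*

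**What the plan says.** The Sample size calculation section sets the common terms. On the test: "All calculations are two-sided and based on an alpha of 5% and a power of 80" per cent. On the effect: "Sample size calculations are based on a 20% improvement from baseline in the control group and 50% improvement in the intervention group". It aims for 410 patients from 20 practices and says that this total reflects clustering and also "allows for 80–85% patient follow up and a 15% practice attrition rate".

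The Cholesterol subsection gives 57% of patients above 5 mmol/l and an ICC of 0.06, and concludes: "A sample size of 410 patients from 20 practices is needed to show a significant improvement in the proportion of patients with a cholesterol" below that limit. This is the largest of the four requirements and equals the trial target.

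The Well-being scores (WBS) subsection states: "A sample size of 221 patients from 12 practices is needed to show a clinically significant difference in WBS". Its inputs are "a mean difference of 5 points, standard deviation, 10.3; ICC of 0.07".

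The abstract and the Primary outcomes list name blood pressure, total cholesterol, HbA1c and the well-being score as primary outcomes.

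**The concern.** The protocol prints everything needed to check these figures: baseline proportion, effect, ICC, number of practices, alpha, sidedness and power. For cholesterol and well-being they do not agree with the sample sizes given. An ICC of 0.06 or 0.07 with about 20 patients per practice more than doubles the unclustered sample size, and the stated totals are too small to have absorbed that in full.

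Cholesterol sets the size of the trial, so the error is not hidden by a larger requirement elsewhere. If power is really about 68%, the chance of missing the planned effect is about 32% rather than 20%, and over 40% after the losses the protocol allows for. A null cholesterol result would then be read as stronger evidence of no effect than the design supports. The primary outcomes also feed the planned cost-effectiveness ratios.

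**Working it through.** **Inputs.** Two-sided alpha 0.05 and power 0.80; 20% against 50% improvement (Sample size calculation). Cholesterol: 57% above 5 mmol/l, ICC 0.06, 410 patients, 20 practices. Well-being: difference 5, SD 10.3, ICC 0.07, 221 patients, 12 practices. Allocation 1:1 is assumed, as no ratio is stated.

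**Cholesterol: trying to reproduce 410.**

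1. Proportions above the limit at follow-up: 0.57 × 0.80 = 0.456 (control) and 0.57 × 0.50 = 0.285 (intervention). Difference 0.171, mean 0.3705.
2. Unclustered n per arm = [1.96·√(2·p̄·(1−p̄)) + 0.8416·√(p1(1−p1) + p2(1−p2))]² / (p1−p2)² = [1.96 × 0.6830 + 0.8416 × 0.6722]² / 0.171² = 124.0, or 248 in total.
3. Design effect = 1 + (m−1) × 0.06. With m = 410/20 = 20.5 it is 2.17; with m = 21 it is 2.20.
4. Required total: 248.0 × 2.17 = 538, or 248.0 × 2.20 = 546 (26 practices of 21).

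Other two-sided versions do not give 410 either:

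| Version (m = 20.5) | Total needed |
|---|---|
| Pooled variance | 538 |
| Unpooled variance | 526 |
| Continuity correction | 588 |
| Improvement applied to the 43% already controlled (51.6% v 64.5%) | about 990 |
| 20% v 50% of all patients improve | about 169 |

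With a two-sided pooled test, 410 would follow from an ICC of (410/248 − 1)/19.5 = 0.033, about half the quoted value.

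**Cholesterol power at the stated size.** Effective n per arm = 410/(2 × 2.17) = 94.5. Power = Φ[(0.171 × √94.5 − 1.96 × 0.6830)/0.6722] = Φ(0.481) = 68.5%. With 420 patients (20 × 21) it is 68.9%. A t reference on 18 df lowers the figure at 410 to about 63–65%, depending on the approximation.

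**After the planned losses.** From 420, with 17 practices left (15% lost) and 80–85% follow-up: 420 × 0.85 × 0.80 = 286, or 420 × 0.85 × 0.85 = 303. Power is 57.4% and 58.6%. Starting from 410 gives 56.9% and 58.2%. With patient loss only and all 20 practices kept, 328 to 348 patients give 64–65%.

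**Detectable effect.** With 20% improvement in control, 80% power needs about 54% improvement in intervention at 410 patients and about 58% after both losses, against the planned 50%.

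**Well-being.**

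1. n per arm = 2 × (1.96 + 0.8416)² × (10.3/5)² = 66.6, or 133.2 in total.
2. m = 221/12 = 18.42; design effect = 1 + 17.42 × 0.07 = 2.219.
3. Required total: 133.2 × 2.219 = 296, not 221.
4. Power at 221 from 12: effective n per arm 49.8; (5/10.3) × √(49.8/2) = 2.422; Φ(2.422 − 1.96) = 67.8% (59% with t on 10 df).
5. Power at 410 from 20: design effect 1 + 19.5 × 0.07 = 2.365, effective n per arm 86.7, power 89%. After both losses it is 80–82% (about 75–76% with a t reference).

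**Control check.** The same method finds the other two figures adequate on their own inputs: about 85% for systolic pressure at 400 from 20 and about 89% for HbA1c at 130 from 8. It does not fail every figure.

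**The case against.** The best defence is that a one-sided 5% test nearly reproduces the numbers. With the quoted ICC of 0.06 it requires 409 (unpooled, 20 per practice) to 423 (pooled, 20.5 per practice) for cholesterol, with 78.9% power at 410. For well-being it requires 233, with 78.1% power at 221. It uses the quoted ICCs unchanged and comes close on both outcomes, so it may explain the figures better than a mistaken ICC. It does not rescue them, because the protocol says in terms that every calculation is two-sided. The cause stays an inference; the contradiction does not.

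Four further points limit the finding.

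- Well-being is not underpowered in the trial as run, since nobody recruits 221 from 12 practices. This stands: the 221 is a wrong printed figure, and the practical harm falls on cholesterol.
- The Cholesterol subsection does not restate the effect, whereas the systolic pressure subsection refers back to it. The effect used here is therefore carried over from the parent section. That section states it generally, and none of the alternative readings tried gives 410.
- The 57–59% applies both losses in full, and the protocol expects lower attrition from earlier experience. That is fair, but with no loss at all power is still only 68–69%.
- The correction is one of wording and concerns one of four primary outcomes. This bears on the cost of the change, not on whether the stated power is right.

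**Conclusion.** The concern holds. On the protocol's own inputs, cholesterol needs about 538 to 546 patients (526 with an unpooled variance) against the stated 410. Power is about 68–69% with complete follow-up and 57–59% after the losses the protocol says it has covered. There is no allowance for loss in this outcome: 410 is given as the number needed, and recruitment yields at most 420. The well-being figure should be about 296 at 18 per practice, but well-being has about 89% power at the trial's actual size. The statement that all calculations meet 80% power is therefore wrong for cholesterol in the trial as planned, and wrong for well-being at the size printed.

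This rests on 1:1 allocation, equal practice sizes, the quoted ICCs, and improvement read as a relative fall in the proportion above 5 mmol/l. The headline powers use the normal approximation; a t reference with practice-based degrees of freedom makes them lower.

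**What to change.** Correct the Sample size calculation section and its Cholesterol and Well-being subsections:

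- State cholesterol power at 410–420 patients from 20 practices as about 69% with full follow-up and 57–59% after the planned losses, and remove the claim that 410 gives 80% and also covers attrition.
- Replace 221 by about 296 patients at 18 per practice, or give well-being power at the real trial size: about 89%, and 80–82% after losses.
- If the original calculations were one-sided, say so and drop the statement that they were two-sided. The planned two-sided power must still be reported as above.

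The cost is wording only, with a less favourable stated power. No extra recruitment is asked for. Within 20 practices, 80% power would take about 46–47 patients per practice before loss, which is inefficient; the direct way to restore it would be about 26 practices of 21, again before loss. Analysing mean cholesterol adjusted for baseline might recover some power. The protocol gives no cholesterol SD, target difference or baseline correlation, so that gain cannot be shown here and the correction does not depend on it.
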